### Data analysis

A detailed statistical analysis plan will be developed in collaboration with an academic statistician prior to the start of the data analysis. Here we describe the key elements. Differences in continuous demographic variables at baseline between intervention and control group will be presented as means ± SD and tested using independent t-tests for normally distributed data. Non-normally distributed variables will be presented as median and range and will be analysed by non-parametric tests. For categorical variables, proportions will be presented and differences will be analysed by chi-square test. Effectiveness with regard to primary and secondary outcomes will be analysed by mixed-effect regression analyses with two levels (individual and school) with data at T1 or T2 as outcomes, according to the principle of intention to treat. We will first test a crude model for all outcomes at T1 or T2 with group as the predictor and adjusted for baseline values of the relevant outcome. In a second step, sex and parental SEP will be added to the model. Interaction between group and sex or group and parental SEP will be tested and analyses stratified if significant interaction terms are found. All children with measurements at T0 will be included and missing data will be handled with multiple imputation. The effect that any missing data might have on results will be assessed by performing sensitivity analyses of augmented data sets. Analysis will also be performed per protocol including only those children whose parents have attended at least one MI session.

Subgroup analyses will be performed with regard to baseline BMI status (underweight plus normal weight, overweight, obesity) and waist circumference (dichotomised). In addition quantile regression will be performed to detect differential intervention effects according to baseline BMI quartiles. The hypothesis behind the subgroup analysis is that children with a high BMI at baseline will respond with a decrease in BMI in contrast to children with lower BMI. Regarding physical activity (TPA, MVPA and time spent sedentary) outcomes will be adjusted for accelerometer monitor wear time.

Mediation analysis will be performed according to MacKinnon [66] with parental self-efficacy and parenting practices, including modelling, as the hypothetical mediators, to see if the programme works according to its theory, and whether effects are moderated by child sex or SEP. All statistical analysis will be performed blinded to group allocation.

Interviews and focus groups will be transcribed verbatim and analysed using qualitative content analysis [67].

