**Methods:**

Effectiveness of the intervention is compared to standard care within school health services. The 6-month programme, based on Social Cognitive Theory, consists of four components: 1) Health information to parents regarding the child; 2) Motivational Interviewing with the parents by the school nurse concerning the child; 3) classroom activities for the children by teachers; and 4) a web-based self-test of type-2 diabetes risk by parents. Effects will be studied in a cluster randomised trial including 17 schools and 352 six-year old children. The primary outcome is dietary intake of indicator foods, and secondary outcomes are physical activity, sedentary behaviour and BMI. Outcomes will be measured at baseline, at 6 months directly after the intervention, and at follow-up 18 months post baseline. Statistical analysis will be by mixed-effect regression analysis according to intention to treat and per protocol. Mediation analysis will be performed with parental self-efficacy and parenting practices. Quantitative and qualitative methods will be used to study implementation in terms of dose, fidelity, feasibility and acceptability. The hypothesis is that the programme will be more effective than standard care and feasible to perform in the school context.

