### Study design

The Healthy School Start Plus study will be conducted as a cluster-randomised parallel trial with randomisation at school level, with a wait-list control group. Simple randomisation of schools to the intervention or control group with a 1:1 allocation ratio was done using a computer-generated randomisation procedure by a statistician not involved in the study. As all school nurses in the intervention group had to undergo training in Motivational Interviewing (MI), something that takes a few months to reach a certain level of competence, randomisation took place before the baseline measurements in order to allow time for this training. However, allocation of schools to intervention or control was only revealed to headmasters, school nurses and the project leader, until baseline measurements done by research assistants, were finalised. Only then were teachers and parents informed. Baseline data was collected in September–October 2017 (T0) from 352 children. Data will again be collected 6 months after the baseline at the end of the intervention in April–May 2018 (T1) and at follow-up in April–May 2019 (18 months post baseline, T2). As an incentive to retain participants in the study, each family will receive a coupon for a healthy meal at a shopping centre restaurant. Mediators will also be measured on one occasion during the intervention, in February 2018 (TM). After the T2 measurement the control schools will be offered the intervention, including MI-training of the school nurses.

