### Sample size calculation

Dietary intake of unhealthy foods is the primary outcome. In our previous study [10], the intake of unhealthy foods was 1.7 ± 2.0 portions/day. We now aim for a difference in intake of unhealthy foods of 0.8 portions/day between the intervention and the control group. Sample size calculation was done according to Twisk [68]. With a power of 80% and significance level of 5% and an intra-class correlation coefficient of 2% (clustering at school level), we need to recruit at least 17 schools with 15 children in each school, 255 children in total.

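### Baseline arm differences are to be tested at child level, ignoring school, so the p-values are too small for any variable that clusters by school (minor; baseline table only)

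*Protocol article*

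**What the plan says.** The Study design section describes a "cluster-randomised parallel trial with randomisation at school level". The abstract gives its size: a "cluster randomised trial including 17 schools and 352 six-year old children". The Sample size calculation allows for this clustering by assuming "an intra-class correlation coefficient of 2% (clustering at school level".

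The Data analysis section then sets out the baseline comparison. It begins: "Differences in continuous demographic variables at baseline between intervention and control group will be presented as means ± SD". These differences are to be "tested using independent t-tests for normally distributed data", and variables that are not normally distributed go to non-parametric tests. For categorical variables, "proportions will be presented and differences will be analysed by chi-square test". School does not appear in any of these tests.

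The same section does use a two-level model, child within school, but only for effectiveness on the primary and secondary outcomes. Those models adjust for the baseline value of the outcome. Sex and parental socioeconomic position (SEP) are added in a second step.

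**The concern.** An independent t-test or an ordinary chi-square test treats every child as a separate draw. Here whole schools were allocated, so children in one school share an arm and may also resemble one another. If they do, the between-arm difference varies more by chance than the test allows for. Its standard error is understated and its p-value is too small on average. The protocol recognises this for the sample size and for the outcomes, but not for the baseline comparison.

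The baseline table matters more than usual in this trial. Schools were randomised before baseline measurement. Headmasters, school nurses and the project leader knew the allocation while baseline data were being collected (Study design). The article's Discussion names this ordering as a weakness. Readers will therefore look to the baseline table for signs of differential recruitment, and tests that overstate imbalance could suggest a problem in a sound trial.

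**Working it through.** **Inputs from the protocol article.**
- 17 schools and 352 children enrolled, a mean of 352/17 = 20.7 per school (abstract).
- Planned 15 children per school, 255 in total; ICC 0.02; SD 2.0 and difference 0.8 portions/day; power 80%; significance level 5% (Sample size calculation).

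**Assumptions.** Two-sided testing; 8 schools against 9; ICCs other than 0.02, since none is given for any demographic variable.

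**1. The plan's own sample size.** Per arm without clustering: 2 × [2.0 × (1.960 + 0.842) / 0.8]² = 98.1. The design effect is 1 + (15 − 1) × 0.02 = 1.28. Total: 2 × 98.1 × 1.28 = 251, and 251/15 = 16.7 schools. Rounded up, this is 17 schools and 17 × 15 = 255 children. The stated figure reproduces, so the plan does use the school ICC in this way.

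**2. Rejection rate of a test that ignores school.** With m children per school, the design effect is DE = 1 + (m − 1) × ICC. The true variance of the between-arm difference is DE times what the test assumes. A nominal 5% test then rejects a true null with probability 2 × [1 − Φ(1.96/√DE)].

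At the stated ICC of 0.02:
- m = 15: DE = 1.28, rejection rate 8.3%.
- m = 20.7: DE = 1 + 19.7 × 0.02 = 1.39, rejection rate 9.7%.

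**3. Range over assumed ICCs at m = 20.7.**

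| ICC | DE | Formula | Simulation |
|---|---|---|---|
| 0 | 1.00 | 5.0% | 4.9% |
| 0.01 | 1.20 | 7.3% | not run |
| 0.02 (stated, for diet) | 1.39 | 9.7% | 10.1% |
| 0.05 (assumed) | 1.99 | 16.4% | 17.0% |
| 0.10 (assumed) | 2.97 | 25.5% | 25.7% |
| 0.20 (assumed) | 4.94 | 37.8% | 38.8% |

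The simulation ran child-level t-tests on 352 children in 17 schools of 20 or 21 (8 schools against 9), with 8,000 runs per ICC. The same design effect applies approximately to a chi-square test of a two-class variable. For country of birth, which has three classes, the direction is the same but the figures differ somewhat.

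**4. Does anything later depend on these tests?** No. The Data analysis section puts the baseline value, sex and parental SEP into the effectiveness models unconditionally, and those models include school as a level.

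**The case against.** Several points on the other side are sound.

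- **Size.** A reader might infer that these tests will flag imbalance far too often. The documents do not support that. Their only ICC is 0.02, it belongs to dietary intake, and it gives 8% to 10%. Education, employment and country of birth may well cluster more. On the other hand, eligibility was limited to schools where fewer than half of parents had university education, which may narrow the spread between schools. The documents do not settle the ICC of any demographic variable. For one with an ICC near zero, possibly child sex, the test is about right.
- **Consequence.** A reader might also infer that the tests will steer covariate choice or distort the estimated effect. Nothing in the Data analysis section makes adjustment conditional on a baseline test.
- **Purpose.** It is often said that baseline tests in a randomised trial only ask whether chance did what it must have done. That is incomplete here. Parents were recruited between May and September 2017, and nurse training was to be finished by August/September 2017. Recruitment may therefore have overlapped with known allocation, and a baseline comparison could reveal selective enrolment. This is a reason to account for school in any test, not a defence of ignoring it.

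The promise of a later detailed analysis plan does not remove the point, because the protocol names the tests itself.

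**Conclusion.** The point holds in a limited form. The planned baseline tests ignore the unit of randomisation, and their p-values are too small for any variable with a positive school ICC. At the protocol's own ICC the nominal 5% becomes about 8% to 10%, which is up to roughly double. That figure borrows a dietary ICC for demographic variables. Rates of 16% to 38% rest entirely on assumed ICCs of 0.05 to 0.20.

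The harm is confined to interpretation of the baseline table. The effectiveness analysis and the sample size are not affected. Severity is minor. Confidence is high that the tests are wrong for this design, and lower on the size for any particular variable.

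**What to change.** Remove the baseline significance tests from the Data analysis section and carry that into the statistical analysis plan. Report means with SD (or medians with range) and proportions by arm, with standardised differences, at child level and at school level.

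If a test is kept to look for differential recruitment, say so and use one that accounts for school: a school random effect with small-sample degrees of freedom, about 17 − 2 = 15.

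The cost is a change of wording. It needs no new data, and dropping the tests reduces the analysis work.

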### Outcome evaluation

All questionnaires are filled in via the project website (www.enfriskskolstartplus.se) with personal accounts for each family. The website has been developed by the research team in collaboration with IT consultants. One member of the research team is appointed administrator of the website. For parents who cannot or do not want to use the website, paper versions will also be available. In order to increase the response rate to the questionnaires, weekly reminders are sent out via e-mail and text messages. Parents are also offered support to log in to the website and if problems arise when responding to the questionnaires.

All outcomes are assessed as the difference between the intervention and the control group directly after the end of intervention at 6-months post baseline, and at follow-up 18 months post baseline, adjusted for baseline values. All outcome and mediator variables, indicators, instruments used and time points of assessment are listed in Table 3.

**Table 3 Tab3:** Overview of outcome and mediator variables, indicators, instruments and time points of assessment

Variables	Indicators and instruments	Time point of assessment^a^
Demographic data parents	Sex, age, country of birth, years in Sweden, level of education, housing conditions, employment, weight, height, number of children	T0
Child’s diet	Child Eating Habits Questionnaire EQ [73] Revised version of Eating and Physical Activity Questionnaire (EPAQ) [53] Mobile phone based photo method based on Delisle et al. [54]	T0, T1, T2
Child’s physical activity and sedentary behaviour	Accelerometry Questionnaire: Active transport, activity in organisation, screen time on week days and weekends	T0, T1, T2
Child’s sleep	Revised version of Eating and Physical Activity Questionnaire (EPAQ) [53]	T0, T1, T2
Child’s BMI	Height and weight measured with instruments (SECA)	T0, T1, T2
Child’s waist circumference	Measured with instruments (SECA)	T0, T1, T2
Parental self-efficacy	Revised instrument based on Wright et al. [63]	T0, (TM), T1, T2
Parental feeding practices	Comprehensive Feeding Practices Questionnaire [64]	T0, (TM), T1, T2
Parenting practices regarding children’s physical activity	Items derived from item bank by Masse et al. [65]	T0, (TM), T1, T2
Nurses’ self-reported MI competence	Revised version of self-rating questionnaire based on MITI 4 [49]	TM
Parent-report of nurse’s MI competence	Revised version of self-rating questionnaire based on MITI 4 [49]	TM

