#### Primary outcomes

The primary outcome is intake at home of a composite score of indicator foods of importance for energy-balance and health, namely fruit and vegetables (healthy foods) and unhealthy foods (sweets, ice cream, buns/cakes, crisps) and unhealthy drinks high in added sugar (sugar-sweetened beverages). Intake of indicator foods was chosen as the primary outcome because our previous studies in comparable population samples showed that diet was a discriminating factor between different socioeconomic and ethnic groups [6] and also improved as a result of the intervention [10, 12]. Intake will be assessed using food frequency questionnaire, the Children’s Eating Habits Questionnaire (CEQ) which measures intake retrospectively in the home during the preceding month, and shows good reliability [52]. This food frequency instrument has been specifically designed for parents of children aged 2–11 years in eight European countries including Sweden and aims to investigate dietary behaviour and the family food environment. In addition, a revised version of the Eating and Physical Activity Questionnaire (EPAQ) will be used [53]. It measures the child’s intake of indicator foods in the home environment during the previous week, and is a semi-quantitative food frequency questionnaire, and includes portion size both in written text and in pictures. The original EPAQ measured intake during the previous day only and was validated against a 24-h recall in an Australian setting with parents of two to five-year-old children [53]. We will also use a new smartphone-based method to estimate the intake of indicator foods eaten at home (volume and frequency) prospectively through standardised photos taken by parents over two weekdays and one weekend day. This method constitutes a further development of the method developed by Delisle et al. [54]. Newer technology-based methods show promise for improving the accuracy of food records [55]. A relative validation study will be conducted in parallel during baseline, where all methods will be compared to multiple 24-h recalls conducted by independent dietitians as the reference method. Our intention is to use the photo-based method for the primary outcome in the intervention study if shown to be valid. The EPAQ will be used for comparison with our previous studies [10, 12].

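### The primary dietary outcome is tested at both 6 and 18 months and neither is named primary, although the trial was sized on a single 5% comparison

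*Protocol article*

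**What the plan says.** The Outcome evaluation section of the protocol article applies one rule to every outcome, primary and secondary: the difference between arms is assessed "at 6-months post baseline, and at follow-up 18 months post baseline, adjusted for baseline values". Data analysis then specifies "mixed-effect regression analyses with two levels (individual and school) with data at T1 or T2 as outcomes". A crude model adjusted for the baseline value comes first, and sex and parental socioeconomic position are added in a second step. These are separate models for each time point, not one repeated-measures model with a named contrast.

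The section on primary outcomes defines what is measured and with which instruments, but not when the deciding measurement is taken. The Sample size calculation section gives the target: "We now aim for a difference in intake of unhealthy foods of 0.8 portions/day between the intervention and the control group". It attaches no time point to that difference, and sets the design parameters as "With a power of 80% and significance level of 5% and an intra-class correlation coefficient of 2% (clustering at school level").

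Data analysis also says that a detailed statistical analysis plan will be written before analysis starts and that the article gives only the key elements.

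**The concern.** A trial sized on one test at 5% should have one test that decides the primary question, or a rule linking the tests it has. Here the primary outcome is tested twice, with no order between the tests and no statement of what counts as success. A significant result at 6 months only, at 18 months only, or at both could each be presented as a positive primary result. The error rate of that combined claim is then above the 5% on which the trial was sized.

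The gap matters in practice because the Background section reports that most benefits in the earlier trials had gone by the 5-month follow-up. If T1 and T2 disagree again, the article does not say which one decides whether the programme works.

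**Working it through.** **Inputs from the article**

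- Standard deviation 2.0 portions/day: "the intake of unhealthy foods was 1.7 ± 2.0 portions/day".
- Target difference 0.8 portions/day, significance level 5%, power 80%, intra-class correlation 0.02, 15 children per school (Sample size calculation).
- Allocation 1:1 by school; 352 children with baseline data in 17 schools (Study design and Abstract).

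**Assumed, because the article does not give them**

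- Each T1 and T2 model is tested at two-sided 5%. The 5% appears only in the sample size section, without sidedness.
- The correlation between the T1 and T2 test statistics is varied from 0 to 0.9.

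**Step 1: reproduce the plan's figure**

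- Per arm, before clustering: n = 2 × [SD × (1.960 + 0.842) / difference]² = 2 × (2.0 × 2.802 / 0.8)² = 98.1, rounded up to 99.
- Design effect: 1 + (15 − 1) × 0.02 = 1.28.
- Total: 2 × 99 × 1.28 = 253.4. Divided by 15 this is 16.9 schools, so 17 schools and 17 × 15 = 255 children.

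The stated 255 is reproduced. A one-sided 5% test would give about 200. So 255 corresponds to one two-sided comparison at 5%, with no alpha split. Power at 255 is 80.6% (normal approximation).

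**Step 2: error rate if either time point may be claimed**

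For independent tests: 1 − 0.95² = 0.0975. For correlated tests: 1 − P(|Z₁| < 1.96 and |Z₂| < 1.96), with Z₁ and Z₂ bivariate normal.

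| Assumed correlation | Chance of at least one false positive |
|---|---|
| 0 | 9.75% |
| 0.3 | 9.5% |
| 0.5 | 9.1% |
| 0.7 | 8.35% |
| 0.9 | 7.0% |

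The rate is above 5% for any correlation below 1.

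**Step 3: what each remedy would cost**

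- One primary time point, the other tested only after it: alpha stays at 5% and N at 255.
- Both primary with Bonferroni at 0.025 each: 119 per arm, and 2 × 119 × 1.28 = 304.6, so 21 schools and 21 × 15 = 315 children. At 0.025, power is 72.0% with 255 children.
- With the 352 children enrolled, the mean cluster size is 352 / 17 = 20.7 and the design effect 1 + 19.7 × 0.02 = 1.394. Power at 0.025 is then about 82.6%, assuming no dropout.

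**The case against.** The strongest reply is that this is a condensed article. It announces a detailed analysis plan, and multiplicity rules commonly belong there. That is right about the adjustment method: its absence alone would be no finding. It does not cover the time point. When the outcome is measured is part of what the primary outcome is, and a target of 0.8 portions/day is incomplete without it. The article does describe the tests it considers key, and they are two of equal rank.

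A second reply is that no section says success at either time point suffices. That also stands. The figures of 7.0% to 9.75% depend on such a rule, on testing each model at 5%, and on an assumed correlation. If both time points had to be significant, or one were primary, the rate would not exceed 5%. The article states none of these rules.

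A third reply is that the article hints at T1, since Table 1 lists dietary intake among the short-term outcomes and Study design calls T2 a follow-up. But Table 1 does not tie that label to T1, Table 3 measures diet at both T1 and T2, and the Background section gives sustained effects as the reason for strengthening the programme. The cues point both ways.

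Finally, a real effect that is present at T1 and fades by T2 is not a false positive. Fading bears on how discordant results would be interpreted and adds nothing to the type I error calculation.

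**Conclusion.** The point holds in this form: the primary time point is not designated, the primary outcome is tested at two time points of equal status, and the sample size allows for one. If a significant result at either may be claimed, the error rate lies between 7.0% (assumed correlation 0.9) and 9.75% (independent tests), instead of 5%.

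Three stronger readings are not supported.

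- A reader might infer that the sample size is wrong. It is not: 255 is correct for the single comparison it describes.
- A reader might infer that the choice of dietary instrument is open as well and adds further tests. The article ranks the instruments. On the photo-based method it says "Our intention is to use the photo-based method for the primary outcome in the intervention study if shown to be valid", the Discussion names the eating habits questionnaire as the fallback, and the EPAQ serves comparison with the earlier studies. The validation study runs on baseline data.
- A reader might count four primary tests, because the outcome is a composite in one section and unhealthy foods in another. No section plans to test both. That mismatch is a separate inconsistency in the outcome definition.

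**What to change.** Before any comparison by arm, add one paragraph to the protocol or the dated analysis plan that:

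1. names T1 or T2 as the time point of the primary outcome and of the 0.8 portions/day difference;
2. states that the other time point is tested at two-sided 5% only if the first is significant;
3. states that a claim of effectiveness on the primary outcome rests on the named time point.

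The choice is for the sponsor. T1, the end of the intervention, fits Table 1's placing of diet among the short-term outcomes. T2 fits the aim of sustained effects. Either is defensible if fixed in advance.

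The fixed sequence costs no alpha and leaves the sample size at 255. Its small downside is that the second time point cannot be confirmatory if the first fails, though its estimate and confidence interval can still be reported. If the sponsor wants both time points to be able to succeed independently, the alpha must be split, at the cost in children or power shown in step 3 of the working.

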## Background

Childhood obesity has been high on the public health agenda for two decades now and while the rapid increase in prevalence seen in the 1990s in the Nordic countries seems to have levelled off to about 3% in Sweden at the population level [1], huge social inequalities persist [2]. According to data from all 4-year-olds in Stockholm County born in 2012, collected through child health care services, the obesity prevalence varies from zero in the most well-off area to over 5% in the most disadvantaged [3]. The explanation for this gradient in younger children does not seem to be due to lower physical activity [4], but can to a large extent be explained by more unhealthy dietary habits in families with low levels of education [5] and of non-Nordic origin [6]. In adolescents, overweight and obesity often result in body image dissatisfaction, poorer self-assessed health status, social isolation, and decreased life satisfaction [7]. In addition, in high-income countries a negative association exists between educational attainment and obesity, particularly in women [8]. Although children in pre-school age [9] and early school-age [10] seem to be adequately physically active there is a clear decrease in physical activity with increasing age [11]. Evidence from Sweden [10, 12, 13] and elsewhere [14] suggest that children are less physically active in the home environment, e.g. during weekends.

When it comes to adults, higher rates of obesity and low physical activity are found in groups with low socio-economic position (SEP), and it has been speculated that these factors are the main causes behind the higher prevalence and earlier onset of type-2 diabetes (T2D) among adults with low SEP [15]. Furthermore, studies have shown that immigrants to Sweden have a significantly higher risk of T2D than Swedish-born individuals even when adjusted for established risk factors [16]. Today it is recognised that development of both obesity and T2D is driven by interacting genetic and environmental factors and is preventable to a large extent [17]. Because health-related behaviours and obesity often track from childhood to adulthood [18, 19], interventions should start from an early age and target the whole family.

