### Recruitment of schools, participants and setting

As a first step in the recruitment, key persons in municipalities in the Stockholm region were contacted, such as head school nurses, heads of elementary school, public health practitioners etc. They received a one-page invitation letter explaining the aim and content of the intervention and were invited to contact the project leader for more information. It was emphasised that the aim of the study was to improve health promotion practice in schools, rather than to burden them with extra work. In some cases the project leader was invited to the municipality or to a specific school to present the study to school staff. In other cases, the schools consented to participate and invited the project leader to the first ordinary school meeting with new parents, where parents are introduced to the school routines. Primary schools were eligible to participate if the proportion of parents with university education was less than 50% compared to 57% at national level [38]. Participating schools signed an agreement with the research team. In total 18 schools with 18 school nurses agreed to participate in the study. One school dropped out before recruitment of parents had started because the nurse went on sick-leave. Parents in the remaining 17 schools were subsequently recruited by the research team face-to-face or by telephone. All parents with a child in pre-school class were eligible to participate. Between May and September 2017, the project group was invited to the school’s meeting with new parents, who were informed about the intervention and the study. Written information was translated into the four languages most commonly used (Swedish, English, Somali and Arabic). Informed, written consent to participate in the study was obtained by the research team from all participating parents.

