#### Covariates

Parental educational level and occupation is self-reported. Based on previous experience, we anticipate that a high proportion of parents will have a non-Swedish background and therefore a composite measurement of SEP is likely to be more appropriate. The composite measurement will consist of the highest level of education attained, and the occupation (according to Statistics Sweden) by either of the parents. A dichotomised variable indicating low and high SEP will be created. Parents will also be asked to indicate their country of birth as well as number of years living in Sweden. Country of birth will be classified as “Sweden/the Nordic region”, “Europe” or “outside Europe”. In addition, child sex will be used.

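### Parental country of birth is declared a covariate and cited as a determinant of diet, but the adjusted model (baseline outcome, sex, SEP) leaves it out without a reason

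*Protocol article*

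**What the plan says.** Under Covariates, the protocol article describes a composite SEP measure (education and occupation, then dichotomised), parental origin, and child sex. On origin it says "Parents will also be asked to indicate their country of birth as well as number of years living in Sweden", and "Country of birth will be classified as" one of three groups: Sweden or the Nordic region, elsewhere in Europe, or outside Europe. Table 3 places this item at baseline (T0).

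The article treats origin as prognostic in two places. The Background attributes much of the social gradient in childhood obesity to unhealthier diets in families with little education and in families of non-Nordic origin. Under Primary outcomes, diet is chosen partly because "diet was a discriminating factor between different socioeconomic and ethnic groups".

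Data analysis sets out two models for every outcome. The first has group and the baseline value of that outcome. For the second: "In a second step, sex and parental SEP will be added to the model". The planned interactions are with sex and SEP, the subgroups are by baseline BMI status and waist circumference, and moderation in the mediation analysis is by sex or SEP. Country of birth appears in none of these.

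Under Study design, schools were allocated 1:1 by simple randomisation, and no stratification is mentioned.

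**The concern.** The section that declares the covariates and the section that uses them do not agree, and no reason is given. The article announces a later statistical analysis plan, but it fixes the covariates of the adjusted model itself. A plan that follows it would therefore leave out a declared covariate.

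SEP does not stand in for the missing variable, because origin is not one of its components. Schools differ in the families they serve, few were allocated, and nothing in the allocation balanced origin. If the baseline table shows a clear difference in origin between arms, the authors will have to report a result not adjusted for it or add a post hoc adjustment that readers may distrust. Specifying the term now avoids that choice.

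**Working it through.** **1. The plan's own figure, to fix the scale.** Inputs from Sample size calculation: SD 2.0 portions/day, difference 0.8, ICC 0.02, 15 children per school, 80% power, 5% significance (taken as two-sided).
- Per arm without clustering: 2 × [2.0 × (1.960 + 0.842) / 0.8]² = 98.1, so 99.
- Design effect: 1 + 14 × 0.02 = 1.28.
- Total: 2 × 99 × 1.28 = 253.4, or 16.9 schools of 15, rounded up to 17 × 15 = 255.

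The stated 255 reproduces. Adding a covariate does not change it.

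**2. Chance difference in origin between arms.** From the documents: 352 children in 17 schools, so m = 352/17 = 20.7. Assumed, because the documents give no figures: 50% of families in the class of interest, between-school SD of that share s = 0.10 to 0.30, and an 8 v 9 split.

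SD of the difference = √[(s² + 0.25/m) × (1/8 + 1/9)]

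| s | SD of difference | chance of a gap above 10 points | above 20 points |
|---|---|---|---|
| 0.10 | 0.072 | 17% | 1% |
| 0.20 | 0.111 | 37% | 7% |
| 0.30 | 0.155 | 52% | 20% |

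An uneven split matters little: at s = 0.20, 6 v 11 schools gives 0.116 instead of 0.111.

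**3. What is left after baseline adjustment.** Let β be the difference in intake by origin (taken as equal at baseline and follow-up), b the slope of follow-up on baseline intake, and d the gap between arms. An imbalance shifts the raw difference by βd. Baseline adjustment removes bβd and leaves β(1 − b)d. Assumed ranges: β = 0.2 to 0.8 portions/day, b = 0.3 to 0.7, d = 0.10 to 0.30.
- Lowest: 0.2 × 0.3 × 0.10 = 0.006.
- Middle: 0.5 × 0.5 × 0.20 = 0.05.
- Highest: 0.8 × 0.7 × 0.30 = 0.168.

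Against 0.8 these are about 1%, 6% and 21%. The highest needs a 30-point gap, which is the 95% limit even at s = 0.30 (1.96 × 0.155 = 0.30).

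**4. Share of the sampling error.** With SD 2.0, ICC 0.02 and m = 20.7, the design effect is 1 + 19.7 × 0.02 = 1.394. The variance of the treatment difference is 4 × 1.394/20.7 × (1/8 + 1/9) = 0.0636 (SE 0.25) before baseline adjustment. At s = 0.20 and β = 0.5, one SD of imbalance shifts the estimate by 0.111 × 0.5 = 0.056 if baseline absorbs nothing, and by 0.028 if it absorbs half. As shares of the variance: 0.056²/0.0636 = 4.9% and 0.028²/0.0636 = 1.2%. The shares rise somewhat if baseline adjustment shrinks the SE.

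**The case against.** The strongest reply is that the plan already deals with most of this. Both models adjust for the child's own baseline intake, which carries much of any effect of origin on diet. Under randomisation, differences between schools in origin are part of the school-level variation that the two-level model is there to reflect. The article also links origin to the choice of SEP measure: it expects that "a high proportion of parents will have a non-Swedish background and therefore a composite measurement of SEP is likely to be more appropriate". Sex and SEP are then used consistently for adjustment, interaction and moderation, and a short covariate list is defensible with 17 clusters.

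Much of this stands. It limits the size of the point, and it means that a chance imbalance should not be called bias. It does not explain why a variable declared as a covariate, and described as prognostic in the same article, is used nowhere. Choosing a composite SEP measure because many families are of foreign background does not put origin into that composite.

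Three stronger readings are tempting, and the documents do not support them.
- A reader might infer that the adjusted model holds only sex and SEP. It also holds the baseline outcome.
- A reader might infer recruitment bias. Randomisation preceded baseline, the first MI training is dated May 2017 under Fidelity, and parents were recruited from May to September 2017, so some recruitment after allocation is likely. It is nowhere stated. Before baseline was complete, "allocation of schools to intervention or control was only revealed to headmasters, school nurses and the project leader", and parents, teachers and research assistants were not told. The project leader attended only some of the parent meetings, and no route is described by which this would shift origin between arms.
- A reader might object that neither model is named as primary. The article may leave that to the analysis plan it announces.

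**Conclusion.** The point holds as an inconsistency with a small, quantifiable consequence. A declared and prognostic covariate is missing from the adjusted model, and SEP does not replace it. Chance imbalance in origin is plausible with simple randomisation of so few schools. The article does not say whether 17 or 18 schools were randomised, since one of the 18 that agreed left before parents were recruited.

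The shift remaining after baseline adjustment is roughly 0.01 to 0.17 portions/day, with a middle value near 0.05, on the sample-size scale where the target is 0.8. The share of foreign-born families, its spread between schools, the effect of origin on intake and the baseline slope are all assumptions. The validity of the trial does not turn on this. The change is still worth making before analysis, because it is specific, nearly free, and removes the need for a later post hoc adjustment.

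**What to change.** Add parental country of birth, in the three classes already defined, to the second-step model for all outcomes alongside the baseline outcome, sex and SEP. Include it in the multiple imputation model as well. The analysis plan will need a rule for families whose two parents fall in different classes. If the investigators prefer to keep the variable descriptive, the protocol should say so and give the reason.

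The cost is two degrees of freedom among 352 children and a few lines of text. The data are collected at T0, so nothing new has to be measured and the sample size is unaffected.
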